### Training

All therapists will be research assistants trained in psychotherapy delivery and supervised by a psychiatrist on the research team who has extensive experience in electronically delivered psychotherapy. All therapists are taught the standard care pathway, the aim, and the content of each therapeutic session. Moreover, they will be provided with sample homework from a previous patient and will be asked to provide feedback as practice. Feedback templates will vary between sessions, and therapists will personalize each template for each patients’ homework. Before feedback is submitted to the participant, it will be read, edited, and approved by a psychiatrist on the research team. Training will occur through webinars and exercises with feedback.

### Outcomes

The primary outcome measure will be changes in activation levels of the basal ganglia and frontal cortex. This will be collected through detectable changes in BOLD values from the fMRI scans at baseline and after treatment (week 16). The secondary outcomes will be changes in symptom severity, quality of life, and functioning. Changes in symptom severity will be evaluated using clinical symptomatology questionnaires (Yale-Brown Obsessive-Compulsive Scale and Obsessive-Compulsive Inventory, Revised) [46,47]. Changes in quality of life will be measured using the Quality of Life and Enjoyment Questionnaire [48]. Changes in levels of functioning will be measured using the Sheehan Disability Scale [49]. All questionnaires will be collected directly through OPTT at baseline, after session 8, and after treatment (week 16).

### Compliance

As with all mental health disorders, treatment compliance is always an area of focus when designing interventions. Participants will have the importance of treatment compliance explained to them during the informed consent process, and participants will need to submit their homework assignments through OPTT before gaining access to their next treatment session. From a previous meta-analysis conducted, the estimated completion rate from in-person psychotherapy is approximately 75% [50]. Additional meta-analyses found treatment adherence for web-based psychotherapy to be between 61% and 66%, with no significant difference with in-person psychotherapy [51-53]. A study investigating the efficacy of a 10-session e-CBT program for OCD had a mean completion of 7.28 sessions [54]. Previous research using OPTT indicated participants completed >8 sessions on average, with over half the participants completing all sessions. In a previous project using e-CBT for patients with generalized anxiety disorder, 90% of participants completed 10-12 weeks of the 12-week program, with over 75% of participants being retained for a 12-month follow-up [55].

### Analysis

For the fMRI data (primary outcome), a 0.5% (eff=0.005) change in BOLD hemodynamic response function will be considered a detectable signal variation between conditions (*P*>10^-6^). An estimated paradigm of expected BOLD response will be created, and the correlation between the real and expected signals will be calculated to detect noise using a general linear model:

S = βX + e **(1)**

Where, S is the time-series data, β is the value for each pattern, X is the set of time-series patterns, and e is the residual.

The general linear model will provide a β value for each term in the basis set and a T value for each β. The BOLD contrast between conditions and scanning periods (ie, baseline and posttreatment) will be evaluated using one- and two-sample *t* tests, assuming a normal distribution. Realignment parameter regressors for the testing conditions will be implemented [56,57]. The effects at each condition will enter a group analysis using a random-effects model [58]. A group-level comparison will be used with small volume corrections performed for multiple comparisons using the Gaussian random field theory. Missing data points can be accounted for in the analysis with usable questionnaires and fMRI data using the linear model.

For questionnaire scores (secondary outcomes), a linear regression analysis will be used to identify variables associated with the outcome measures while controlling for demographic variables (ie, age, sex, and gender). Repeated measures of analysis of variance will be conducted to determine changes between periods (ie, baseline, week 8, and posttreatment) questionnaire scores. Greenhouse-Geisser adjustment for F-statistics and Bonferroni corrections for multiple comparisons will be used. Using the Pearson correlation coefficient, the correlation between the questionnaire score and the BOLD response will be evaluated. Data outliers will be defined as SD 3.29 away from the mean on scores.

Skew and kurtosis will be analyzed assuming a normal distribution in the questionnaire and fMRI data at all collection time points. Age, gender, and sex variables will be considered in knowledge creation and translation.

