The most implicated regions of the brain associated with OCD are the basal ganglia and frontal cortex. These regions are involved in motor control and cognitive functioning tasks, including abstract reasoning, planning, decision-making, and inhibition [31-33]. More specifically, the basal ganglia play a large part in selecting movements that have positive effects [34]. In the case of OCD, it is hypothesized that this could play a part in the compulsive behaviors of OCD (eg, hand washing if cleanliness is an obsession). The frontal cortex is involved in reward processing, impulse control, and emotional control, among others [35]. If we learn that treatment can alter a patient's anxiety processing at a neural level, more specific treatments targeting these brain regions can be developed. Research suggests that in patients with OCD, the basal ganglia and frontal cortex are hyperactive at rest, becoming further activated while in anxiety-inducing situations [13,15,33,36-43]. These studies also suggest that successful treatment may result in a partial reversal of this hyperactivation [13,15,33,36-43]. However, more work is needed to make definitive conclusions on whether activation levels decrease following successful treatment.

By measuring brain activation levels while exposed to neutral and anxiety-inducing stimuli pre- and posttreatment, the suspected regions involved in OCD pathology (basal ganglia and frontal cortex) can be observed. These findings can help explain whether effective treatment results in changes in activation levels, whether symptom improvement is correlated to changes in activation levels, and if there are any treatment response identifiers. If anxiety processing in patients with OCD can be understood better, more targeted treatments altering these specific parts of cognition can be developed. It is currently unknown whether e-CBT can produce these effects.

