### Participants

Participants (n=10) will be recruited from family medicine and psychiatric clinics at Queen’s University and Kingston Health Sciences Centre sites (Hotel Dieu Hospital and Kingston General Hospital) in Kingston, Ontario, Canada. In addition, local and social media advertisements will be used. Participants will be enrolled in the study based on referrals from outpatient clinics and family doctors as well as self-referrals. Those invited and interested in participating will have the study protocol explained and an evaluation done by a psychiatrist on the research team through a secured video appointment. Participants will be evaluated for a diagnosis of OCD based on the *Diagnostic and Statistical Manual of Mental Disorders, 5th Edition* [44]. After a diagnosis of OCD is confirmed and the participant is given written and verbal instructions on how to participate in the study, informed consent will be obtained.

The inclusion criteria include the following: between the ages of 18 and 65 years at the start of the study, a diagnosis of OCD according to the *Diagnostic and Statistical Manual of Mental Disorders, 5th Edition* criteria, competence to consent to participate, ability to speak and read English, and consistent and reliable access to the internet. Exclusion criteria include the following: having any metal implants or additional factors deemed not safe for an MRI scan, active psychosis, acute mania, severe alcohol or substance use disorder, and/or active suicidal or homicidal ideation. In addition, if a participant is currently receiving another form of psychotherapy, they will be excluded from the study.

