The images will be shown in sets (groups of 5 images) as opposed to intermingled, in the hope of producing a more sustained emotional state and allowing for more distinct readings. The ordering of the image sets repeats halfway through (back to back of the anxiety-inducing images in the example above) to control for participants becoming accustomed to image ordering. This ordering will be changed for every participant (ie, the next participant would receive back-to-back sets of the neutral imaging in runs 2 and 3) to counterbalance the imaging sets. Participants will be prompted to imagine themselves in the situations described in the images. The images will appear on a screen that will be reflected into the scanner for participants to view. A 0.5% blood oxygen level–dependent (BOLD) signal difference between conditions (*P*<10^-6^) will be considered a detectable change (eff=0.005).

Anatomical reference images will be captured with the phase-encoding direction collected sagittally from anterior to posterior. These images will be captured with T1-weighted high-resolution magnetization-prepared rapid acquisition gradient-echo (MPRAGE) images with 0.8×0.8×0.8 mm^3^ isotropic voxels. These images will use a 256 mm field of view (FOV), 2500 ms repetition time (TR), 2.22 ms echo time (TE), 8-degree flip angle, and a 320×320 mm matrix resolution. Following this, T2*-weighted gradient-echo echo-planar imaging (GE-EPI) with 3.0 mm 3.0×3.0×3.0 mm^3^ isotropic voxels will be used for the stimuli-exposed image acquisitions in an anterior-to-posterior direction. These images will use a 192 mm FOV, 2500 ms TR, 28.4 ms TE, 90-degree flip angle, and a 64×64 mm matrix resolution. A multiband acceleration factor of 2 will be used, with 170 volumes being captured. Following the GE-EPI imaging, two short spin-echo field map scans will be captured from anterior to posterior and then posterior to anterior. These images will use a 192 mm FOV, 8000 ms TR, 66.0 ms TE, 90-degree flip angle, 180-degree refocus flip angle, and a 64×64 mm matrix resolution. All images will use a bandwidth of 1500 Hz.

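### The detection rule for the primary fMRI outcome is printed with opposite inequality signs, is set on the picture contrast and not on the change from baseline to week 16, and does not say at which level of analysis it applies

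*Protocol article*

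**What the plan says.** The Protocol article states the detection rule twice.

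- Methods, Imaging, for a 0.5% BOLD effect: "signal difference between conditions (*P*<10^-6^) will be considered a detectable change (eff=0.005".
- Methods, Analysis, in the sentence that opens the primary-outcome analysis: "a 0.5% (eff=0.005) change in BOLD hemodynamic response function" "will be considered a detectable signal variation between conditions (*P*>10^-6".

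The Outcomes section names activation change in the basal ganglia and frontal cortex as primary and ties it to detectability across time: "This will be collected through detectable changes in BOLD values from the fMRI scans at baseline and after treatment (week 16".

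The Analysis section then describes a time-series general linear model giving a T value for each coefficient. It continues: "The BOLD contrast between conditions and scanning periods (ie, baseline and posttreatment) will be evaluated using one- and two-sample *t* tests". After that come a random-effects group analysis and a small-volume correction based on Gaussian random field theory. The sample is small: "Participants (n=10) will be recruited".

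**The concern.** Three things are unclear in the rule that is meant to say when the primary outcome has been detected.

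1. **Sign.** The two statements use the same 0.5% and the same eff=0.005 but opposite inequalities. The reversed one stands in the text that governs the primary analysis.
2. **Contrast.** Both statements define detection as a difference between conditions. The Analysis section lists conditions separately from scanning periods, so conditions cannot simply be read as before versus after treatment. The primary outcome nevertheless depends on detectable change from baseline to week 16, and the document gives no other definition of detectable.
3. **Level.** Nothing says whether 0.5% with P<10^-6 applies to a single participant's scan or to the group result.

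The readings differ widely in strictness. If the choice between them were left until the data are in, it could decide what is reported for the primary outcome.

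**Working it through.** **No figure to reproduce.** The article gives no SD, temporal signal-to-noise ratio (tSNR), group significance level or power, so neither n=10 nor the threshold can be re-derived. What can be checked is what each reading of the rule implies.

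**Inputs from the article:** 0.5% effect (eff=0.005), P threshold 10^-6, n=10, image split R=0.5, 170 volumes (whether per run or in total is not stated). **Assumptions:** two-sided tests; for the single-participant check, independent errors and a simple on/off regressor.

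**Step 1: the printed sign.** Under the null, a P value exceeds 10^-6 with probability 1 − 10^-6 = 0.999999, or 99.9999%. The P condition in the Analysis section therefore screens out essentially nothing, and only the 0.5% amplitude cut remains. Taken literally, it would also reject the strongest signals, those with P at or below 10^-6.

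**Step 2: P<10^-6 in one participant's time series.** With t = eff × tSNR × √(N·R·(1−R)) and a two-sided critical z of 4.89:

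- N=170: 0.005 × √(170 × 0.25) = 0.0326, so tSNR must be about 4.89/0.0326 = 150.
- N=680 (170 volumes in each of four runs): 0.005 × √(680 × 0.25) = 0.0652, so tSNR must be about 4.89/0.0652 = 75.

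At this level the threshold depends on scan length and signal quality. The number of participants does not enter.

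**Step 3: P<10^-6 on the group pre-post test, if it were applied there.** For 10 pairs (df=9), the two-sided critical |t| is 11.64. The smallest observed standardised change that passes is 11.64/√10 = 3.68. A mean change of 0.5% would need an SD of individual changes no larger than 0.5/3.68 = 0.136 percentage points. Power from the noncentral t distribution:

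| True standardised change | Power at P<10^-6 | Power at two-sided 0.05, uncorrected |
|---|---|---|
| 1 | 0.07% | 80% |
| 2 | 3.5% | over 99.9% |
| 3 | 27% | over 99.9% |

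Power of 80% at P<10^-6 needs a true standardised change of 4.34.

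**Step 4: which level the text suggests.** The rule comes directly before the time-series model, the eff and R notation suits a first-level calculation, and the group stage has its own correction. This points to a single-participant threshold (Step 2). It is an inference, because the article does not state the level.

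**The case against.** The strongest reply is that the reversed sign is a misprint. The Imaging section has the usable direction, a careful reader will see the slip, and this is a 10-person open-label pilot. On the natural reading, a first-level threshold and a corrected group test are successive stages and do not compete. The pre-post contrast is also planned explicitly among the t tests. Most of this stands. The right contrast is analysed; what is missing is a link between it and the word detectable, and a label for the level of the rule.

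Three stronger readings are tempting, and the article does not support them.

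- *Ten people cannot meet the rule.* Nothing in the article makes 10^-6 the group significance level. Even on that test it is not impossible: an observed standardised change of about 3.7 would pass.
- *The misprinted rule passes everything.* It does not, because the 0.5% amplitude requirement remains under either sign.
- *A real treatment effect must fall below 0.5% and be missed.* The Background section says only that "successful treatment may result in a partial reversal of this hyperactivation". It gives neither the size of the baseline contrast nor the fraction reversed, and 0.5% is a detection floor, not an expected effect. Any figure for the expected change would be the reader's own assumption.

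The reply does not remove the contradiction. An analyst who follows the Analysis section as printed has the wrong threshold for the primary outcome.

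**Conclusion.** The point holds in this form. The rule is wrong as written in the Analysis section, where its P condition is empty (met by 99.9999% of null tests). In both places it is defined between picture conditions, while the primary outcome is the baseline-to-week-16 change, and its level of analysis is not stated. The sign conflict and the mismatch of contrast rest on the text alone and need no assumption.

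The group-level figures (|t| of at least 11.64, standardised change of about 3.7, power 0.07% and 3.5%) are conditional. They assume 10 complete pairs, a two-sided test, and a threshold carried to a test to which the article does not assign it. They show why the level must be stated; they do not show that the planned group analysis will fail.

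**What to change.** 1. In Analysis, change the inequality to P<10^-6, to agree with Imaging.
2. In both sections, state that the 0.5%/P<10^-6 rule is a single-participant, single-session detection threshold for the contrast between anxiety-inducing and neutral images.
3. State that the primary inference is the group-level within-participant change (week 16 minus baseline) in the anxiety-minus-neutral contrast in the two regions. It is to be judged by the random-effects test with small-volume correction already planned, and not by the 0.5%/10^-6 rule. Make the word detectable in Outcomes consistent with this.

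The cost is a few sentences. No new data, scans or participants are needed, and the planned group analysis is unchanged. The sponsor should confirm that the single-participant reading is the intended one and should make the change before the pre-post data are analysed.

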## Methods

### Design

A nonrandomized pilot study design will be used with all participants receiving 16 weekly sessions of e-CBT. Functional magnetic resonance imaging (fMRI) will be conducted at baseline and posttreatment to evaluate activation level changes in the basal ganglia and frontal cortex. Clinically validated symptomology questionnaires will be used to evaluate treatment efficacy. In addition, qualitative interviews will be conducted to gather personal demographic information as well as information regarding participant experience while using the web-based psychotherapy clinic. The pilot study has been registered on the ClinicalTrials.gov Protocol Registration and Results System (NCT04630197). In addition, ethics approval has been obtained from the Queen’s University Health Sciences and Affiliated Teaching Hospitals Research Ethics Board (HSREB; file number 6031276).

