### Imaging

All imaging will occur at the Queen’s University MRI Facility in Kingston, Ontario, Canada, using a Siemens 3.0 Tesla whole-body MRI scanner with a standard coil. Scans will occur at baseline (pretreatment) and after week 16 (posttreatment). During scanning, participants will lie on the scanning table on their backs, with their heads resting on a foam pad to reduce movement. Scanning appointments will take approximately 1 hour per session.

Anatomical reference images will be captured initially. After this, fMRI scans will occur while participants are shown neutral images and anxiety-inducing images (eg, dirty dishes if cleanliness is an anxiety-inducing concept for a specific participant). The frontal cortex and basal ganglia will be the focus of the imaging procedures as their activation level changes during neural anxiety processing are of interest. These images will be standardized pictures from the International Affective Picture System [45]. This large database allows for the selection of images that relate to a variety of obsessions representative of each participant (ie, contamination, sexual thought intrusion, and fear of harm). Each set of pictures will be individually tailored to each participant. These images will be selected ahead of time by a psychiatrist on the research team and will be related to the participant’s anxieties. Participants will be shown a total of 40 images (20 neutral and 20 anxiety inducing; R=0.5) during the fMRI sessions. There will be four fMRI runs that occur in the following sequence:

5 neutral images (30 seconds per image, 5 seconds break between), 1-minute break, 5 anxiety-inducing images (30 seconds per image, 5 seconds break between), 1-minute break.5 new anxiety-inducing images (30 seconds per image, 5 seconds break between), 1-minute break, 5 new neutral images (30 seconds per image, 5 seconds break between), 1-minute break.5 new anxiety-inducing images (30 seconds per image, 5 seconds break between), 1-minute break, 5 new neutral images (30 seconds per image, 5 seconds break between), 1-minute break.5 neutral images (30 seconds per image, 5 seconds break between), 1-minute break, 5 anxiety-inducing images (30 seconds per image, 5 seconds break between).

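### The fMRI analysis names a two-sample t test for contrasts that are all within-participant, and does not say that the two scans are compared as pairs

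*Protocol article*

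**What the plan says.** The Design section describes one treated group: "A nonrandomized pilot study design will be used with all participants receiving 16 weekly sessions of e-CBT". The Participants section sets the size: "Participants (n=10) will be recruited from family medicine and psychiatric clinics". Under Imaging, each person is scanned twice and sees neutral and anxiety-inducing pictures in each session: "Scans will occur at baseline (pretreatment) and after week 16 (posttreatment"). The Outcomes section defines the primary outcome as a change: "The primary outcome measure will be changes in activation levels of the basal ganglia and frontal cortex".

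The Analysis section then names the object to be tested, "The BOLD contrast between conditions and scanning periods (ie, baseline and posttreatment"), and says that it "will be evaluated using one- and two-sample *t* tests, assuming a normal distribution". Shortly afterwards it adds: "The effects at each condition will enter a group analysis using a random-effects model". It does not mention pairing, a difference score or a participant effect for the fMRI data. The secondary questionnaire outcomes do get a method for repeated measurement: "Repeated measures of analysis of variance will be conducted to determine changes between periods".

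**The concern.** A two-sample t test treats its two sets of values as coming from different people. The sentence that names it lists two factors, picture condition and scanning period, and every participant contributes to both levels of both. An analyst who followed the text literally could treat 10 baseline values and 10 week-16 values as 20 independent observations.

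The standard error would then leave out the within-person correlation. In a study of 10 people, pairing may be the main source of precision, and this is the primary outcome. An interval that is too wide could hide a real change in activation. It would also give a poor basis for planning the larger randomized trial that the Results section mentions. If some participants miss the second scan, an unpaired test would compare partly different sets of people, and change would be mixed with selection.

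**Working it through.** **Plan's own figure.** The article gives no power calculation, between-participant SD or scan-to-scan correlation, so there is nothing to reproduce.

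**Inputs from the article.** n = 10 (Participants); one arm (Design); two scans per person (Imaging); change between scans as primary outcome (Outcomes).

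**Assumptions, not from the article.** Equal SD at both scans; bivariate normal values; rho from 0 to 0.7; two-sided alpha of 0.05; a shift of 1 SD for power; no drop-out.

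**Standard errors of the mean change, in SD units.**
- Two-sample: sqrt(2/n) = sqrt(2/10) = 0.447, whatever rho is.
- Paired: sqrt(2(1−rho)/n). At rho = 0.5 this is sqrt(1/10) = 0.316.
- Ratio: 1/sqrt(1−rho). At rho = 0.5 this is 0.447/0.316 = 1.41.

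**95% CI half-widths, in SD units.**
- Two-sample, 18 degrees of freedom: 2.101 × 0.447 = 0.94.
- Paired, 9 degrees of freedom: 2.262 × sqrt(2(1−rho)/10).

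**Type I error and power.** Simulated with 2,000,000 sets of 10 pairs per setting.

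| rho | SE ratio | Half-width, two-sample | Half-width, paired | Type I error, two-sample | Power, two-sample | Power, paired |
|---|---|---|---|---|---|---|
| 0 | 1.00 | 0.94 | 1.01 | 5.0% | 56% | 51% |
| 0.1 | 1.05 | 0.94 | 0.96 | 4.0% | 57% | 56% |
| 0.3 | 1.20 | 0.94 | 0.85 | 2.3% | 57% | 66% |
| 0.5 | 1.41 | 0.94 | 0.72 | 1.0% | 59% | 80% |
| 0.7 | 1.83 | 0.94 | 0.55 | 0.2% | 61% | 95% |

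The paired test keeps its type I error at 5.0% in every row. At rho of 0 to 0.1 the two tests are about equal, and the unpaired one is slightly ahead because it has more degrees of freedom. With a negative correlation the direction reverses: at rho = −0.3 the two-sample test would reject a true null in about 8.3% of trials.

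**The case against.** **The right test may already be in the sentence.** One-sample tests are named too, and a one-sample t test on each participant's difference is a paired test. The random-effects sentence is compatible with that reading. This stands in part. A reader might infer that the plan commits the primary comparison to an unpaired test, but the text does not go that far. It names both tests and leaves the assignment open. It does not say that the one-sample test is meant for the scan-to-scan difference, and the random-effects sentence does not link a person's two scans.

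**Independent groups may be intended.** The Objectives section mentions controls, and the Background and Discussion sections want to identify features of treatment responders, the Discussion also naming nonresponders. So a reader should not conclude that a two-sample test has no possible use in this study. But no controls are recruited, and the Analysis section ties the t tests to conditions and scanning periods, not to such groups. These aims justify restricting the two-sample test, not leaving it where it is.

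**The illustration does not use the plan's threshold.** This is right. The article gives no 0.05 level for the fMRI data. It prints 10^-6, with the inequality sign reversed between the Imaging and Analysis sections, and adds a small-volume correction. At a threshold of 0.001, paired power for a 1 SD shift is only about 9%, 16% and 36% at rho 0.3, 0.5 and 0.7, against 6%, 5% and 4% unpaired. At 10^-6 both are below 1%. The power columns therefore show direction and are not a forecast. The standard-error ratio does not depend on alpha.

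**Drop-out is covered.** The Analysis section says that missing points can be handled through the linear model, but not how. The Compliance section reports adherence to therapy in other studies, with widely differing figures. It does not predict how many participants will return for the second scan, so no number can be put on that effect.

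**Conclusion.** The point holds as a defect in the stated analysis. The two-sample t test fits neither of the comparisons for which it is named, and nothing else in the article says that the two scans are analysed as pairs.

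If the two-sample test were applied to the two scans, the standard error would be too large by a factor of 1.20 to 1.83 for rho between 0.3 and 0.7, and correct at rho = 0. This rests on equal SDs and on an assumed rho. The correlation of the anxiety-minus-neutral contrast between scans could be low, and the gain from pairing would then be small.

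A reader might infer that the plan risks a false claim of effect. With positive correlation it does the opposite: the test is conservative, and the loss is in power and interval width. The consequence is moderate, in a 10-person pilot, but it falls on the primary outcome.

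**What to change.** In the Analysis section, replace the general reference to one- and two-sample tests with an assignment for each comparison:

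- **Baseline to week 16 (primary).** For each participant, take the anxiety-minus-neutral contrast at week 16 minus the same contrast at baseline. Test it with a one-sample (paired) random-effects t test and report a 95% CI. Use participants with both scans, or a model with a participant effect if incomplete pairs are to be kept.
- **Anxiety versus neutral within a session.** Use the same paired form.
- **Two-sample t test.** Restrict it to independent subgroups that the plan defines, such as responders versus nonresponders, or remove it.

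The cost is wording only. No additional participants, scans or data are needed.

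### Gaussian random field correction of the primary fMRI comparison is not reliably 5% at n=10 on 3-mm voxels; a sign-flip permutation test is better calibrated at almost no cost

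*Protocol article*

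**What the plan says.** The Outcomes section of the protocol article sets the target: "The primary outcome measure will be changes in activation levels of the basal ganglia and frontal cortex". The Design section makes this a single treated group: "A nonrandomized pilot study design will be used with all participants receiving 16 weekly sessions of e-CBT". The Participants section gives the size: "Participants (n=10) will be recruited from family medicine and psychiatric clinics". A one-sample test of within-person change therefore has at most 9 degrees of freedom. The Imaging section acquires the functional images at 3 mm in each direction: "isotropic voxels will be used for the stimuli-exposed image acquisitions in an anterior-to-posterior direction".

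In the Analysis section, contrasts between conditions and scanning periods "will be evaluated using one- and two-sample *t* tests, assuming a normal distribution". They enter a random-effects group model, and multiplicity is handled as follows: "A group-level comparison will be used with small volume corrections performed for multiple comparisons using the Gaussian random field theory".

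The article does not say whether the correction applies to voxel peaks or to clusters. It gives no smoothing, region volumes, group-level alpha or between-person SD. An article may leave those details to the full protocol or analysis plan, and their absence is not the point here. The point is the correction method that the article names.

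**The concern.** Random field theory approximates the null distribution of the peak (or cluster size) of a continuous, smooth field. With few degrees of freedom, a t field has heavy tails and narrow peaks that a 3-mm grid does not resolve. The peak formula then predicts higher chance maxima than the voxels can show, so its threshold is too high. The cluster-size formula relies on other approximations and can err the other way.

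The study's main hypothesis rests on this test, and the Results section says that an expanded randomized trial is planned. If the threshold is too strict, a null result may come partly from the formula. If it is too lenient, a positive finding may be spurious. Either could mislead the planning of the later trial.

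**Working it through.** **Inputs.** From the article: n=10, so 9 df; 3-mm voxels; one-sample t test of change. Assumed, because the article does not give them: one-sided family-wise 5%; map smoothness (FWHM) of 6, 8 and 12 mm, that is 2, 2.67 and 4 voxels; box-shaped regions of 150, 729 and 1,100 voxels. One voxel is 0.027 cm³, so these are about 4, 20 and 30 cm³. Effect size d is the mean change divided by its between-person SD. The article gives no power calculation or group threshold to reproduce.

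**Step 1: voxel-level threshold.** Solve Σ R_k·ρ_k(t) = 0.05 for k = 0 to 3. The ρ_k are the Euler characteristic densities of a t field with 9 df. For a cube of side s = 9/FWHM (729 voxels), the R_k are 1, 3s, 3s² and s³. At FWHM 2 voxels, s = 4.5 and R = 1, 13.5, 60.75, 91.125. At t = 9.95 the densities are 1.87×10⁻⁶, 1.28×10⁻⁵, 8.22×10⁻⁵ and 4.91×10⁻⁴. The sum is 0.000002 + 0.00017 + 0.00499 + 0.04471 = 0.050. Bonferroni is the upper 0.05/729 point of t with 9 df, which is 6.32.

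**Step 2: compare with simulated null maps, n=10.** Entries are for 6 / 8 / 12 mm, from 1,000-2,000 null maps per setting.

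| Region | Random-field t | Bonferroni t | Simulated 5% t | True error of random-field rule |
|---|---|---|---|---|
| 150 voxels | 7.49 / 6.40 / 5.14 | 5.08 | 4.99 / 4.76 / 4.18 | 0.2 / 0.6 / 1.9% |
| 729 voxels | 9.95 / 8.52 / 6.84 | 6.32 | 6.25 / 6.00 / 5.57 | 0.2 / 0.75 / 1.45% |
| 1,100 voxels | 10.70 / 9.17 / 7.37 | 6.68 | 6.52 / 6.49 / 5.84 | 0.1 / 0.2 / 1.3% |

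Every random-field threshold exceeds Bonferroni, which is itself valid. Measuring the 729-voxel cube between voxel centres (s = 8/FWHM) lowers its thresholds to 9.34, 7.99 and 6.41, still above 6.32.

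**Step 3: power for a focal change under peak inference, n=10 (6 / 8 / 12 mm).**

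| Focal effect | Random field | Calibrated comparator | Loss in points |
|---|---|---|---|
| 1,100 voxels, d=1.0 in 33 voxels | 7 / 17 / 26% | 69 / 62 / 55% (simulated threshold) | 62 / 45 / 29 |
| 729 voxels, peak d=1.5 | 6 / 16 / 47% | 42 / 51 / 70% (sign-flip) | 36 / 35 / 23 |
| 729 voxels, peak d=2.0 | 20 / 35 / 51% | 85 / 76 / 74% (sign-flip) | 65 / 41 / 23 |

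The first row rests on 200 signal runs, with simulation error of up to about 7 points.

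**Step 4: if the software takes the lower of the random-field and Bonferroni thresholds.** The true error becomes 2.2-4.6% (150 and 1,100 voxels), or 4.7 / 4.1 / 2.7% for 729 voxels. For the d=1.0 focus, power is 68 / 55 / 41% against 69 / 62 / 55%, a loss of 1, 7 and 14 points. Other simulated focal effects lose 13-17 points at 12 mm.

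**Step 5: if inference is on cluster size.** With cluster-forming P of 0.01 or 0.001, the true error is 4.4-11.0% (150 voxels) and 4.9-7.3% (1,100 voxels). With an assumed long-tailed spatial correlation (8,000 voxels, 6-8 mm, 120 runs) it is 11-14% at P=0.01 and 4-8% at P=0.001.

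**Step 6: the alternative.** Full-enumeration sign-flip of the maximum t gave 4-6% family-wise error at n=10.

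**The case against.** A reader might infer that the planned test is far too strict and that a real fall in activation will usually be missed. The article does not support that, for four reasons.

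- **Level of inference.** The Analysis wording fits cluster inference as well as peak inference. At cluster level the error is nominal to too lenient, and power for the d=1.0 focus (82 / 76 / 70% at forming P=0.001) is above that of the simulated peak threshold. The direction of the error therefore cannot be stated as fact.
- **Bonferroni floor.** If the software applies one, most of the loss disappears at low smoothness. The article names only random field theory, so this can be neither assumed nor ruled out.
- **Size and extent of effect.** A fall of d=1.0 across the whole 1,100-voxel region is found in 88 / 97 / 100% of runs even with random-field peaks. A focal fall of d=0.5 is found in only 7-9% of runs with the simulated threshold. Much of the weakness comes from n=10 and the voxelwise search, not from the correction.
- **Number of pairs.** With 6 pairs the figures are starker: for the d=1.0 focus, 0% against 11-14%. But the 61-66% adherence in the Compliance section comes from outside meta-analyses and is not a forecast of paired scans. The same section cites a program in which 90% of participants completed 10-12 of 12 weeks.

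All four stand, and they limit the point. They do not rescue the method: a 5% error rate cannot be relied on under either level of inference.

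**Conclusion.** The point holds in a conditional form. At 9 df on 3-mm voxels, the named correction does not dependably deliver 5%.

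- **Peak inference, 6-12 mm, no floor:** true error about 0-2%, and roughly 20-60 points of power lost for a focal change, depending on smoothness and effect size.
- **Peak inference with a Bonferroni floor:** little loss at low smoothness, about 10-17 points at 12 mm.
- **Cluster inference:** error about 4-11%, so the concern is false positives.

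These sizes rest on the assumed region volumes, smoothness, effect sizes and one-sided 5% level. That the calibration is unreliable did not depend on which of the region sizes was used. The change is worth making because a named method is replaced by a better-calibrated one at negligible cost.

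**What to change.** In the Analysis section, for the one-sample post-minus-baseline contrast, replace the random-field correction with a sign-flip permutation test. Form each participant's change image and flip its sign over all 2¹⁰ = 1,024 patterns. Compare the observed maximum statistic with its permutation distribution inside each pre-specified region mask, at a stated family-wise 5%. State in advance whether the statistic is peak t or cluster size, and for cluster size fix the forming threshold. The same procedure serves both.

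The cost is a sentence or two of wording and slightly more computing, with no added participants, scans or staff. The test assumes that change values are symmetric about zero under the null, which is weaker than the normality already assumed. P values become coarse if few pairs remain. With 6 pairs there are 2⁶ = 64 patterns, so the smallest P is 1/64 = 0.016 one-sided or 2/64 = 0.031 two-sided. The change covers only the one-sample contrast, not the two-sample t tests that the section also names. It does not cure the low power of n=10 for small effects.
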